### 2.2. Data Collection

The baseline data include patient demographic details, such as gender, date of birth, cardiac device type, implantation date, and indication for the device implantation. They also include health conditions (such as a history of hypertension or heart failure) and information on prescription drugs at enrolment, obtained from electronic medical records.

We determined that a historical group is necessary to compare and analyse patients’ hospitalisation rates and satisfaction before and after the application of RM. Patients in the historical group were diagnosed with heart diseases a considerable time before enrolment. They will be compared to patients in the initiating group to determine whether the hospitalisation rate improves with the application of RM.

The two patient groups in this study are as follows: (1) the historical group consisting of patients who already have CIEDs (implanted after January 2020) and have attended outpatient device check-ups (225 patients planned); (2) the initiating group consisting of patients who will undergo CIED implantation after providing informed consent for participation in this study (225 patients planned). We want to investigate the convenience of and satisfaction with RM applications for patients who have yet to experience RM and obtain information on major adverse cardiac and cerebrovascular events (MACCEs) that occurred before RM was applied. Considering the patients’ average lifespan, analysing MACCEs only in the historical group will cause limitations in the future. Therefore, we will also determine the MACCEs in the initiating group for comparison. After informed consent was provided, the patients or their caregivers received a CardioMessenger Smart transmitter (CM) paired with their CIED. The CM collects information through wireless technology (including therapeutic interventions, arrhythmic events, thoracic impedance information, lead data, and device-related alerts), encodes the collected biometric data, and transmits it to a medical institution. Daily RM will be initiated the day after device pairing. In the case of long business trips or other types of extended travelling, patients are asked to take the CM with them and keep it connected to a charger at night near their bedside.

In this study, we may also use the successor model of the CM family. The package provided to participants will consist of the CM and a power supply module. The CM receives information from the paired CIED once daily, typically at night. The transmitter is used for communication with the CIED, and the data received from the device are encrypted and sent to the company website (www.biotronik-homemonitoring.com/, accessed on 6 February 2025) via the data module. Healthcare providers receive an alert from the website when the device detects a change in the patient’s heart rhythm, identifies issues with the device itself, or prompts a reminder for periodic, overall CIED check-ups.

The ReVe study will be the first prospective multicentre study in South Korea in which the following conditions are fulfilled:(1)Collecting data from all visits or admissions during the study period, classified as device-related, patient cardiovascular condition-related, or non-cardiovascular condition-related events. These visits will also be categorised as either physician-driven (RM-based) or patient-driven hospital visits.(2)Analysing MACCEs, such as myocardial infarctions/cerebrovascular accidents, thromboembolic events, exacerbation of heart failure, admissions due to cardiac causes, cardiac-related mortality (as a proportion of overall mortality), and other cardiac events.(3)Collecting and analysing data on RM variables weekly, including thoracic impedance and lead sensing, to elucidate their correlation with disease progression, admission, and mortality.(4)Evaluating the staffing/time requirements for RM using electronic medical records (log-in and log-out times are recorded).(5)Analysing and comparing patient satisfaction questionnaires after RM every 6 months (Table 1) via telephone or during office visits (between the historical and initiating groups). The questionnaire evaluates the efficacy of RM and the perceived quality of care due to RM. It contains nine questions with five answer categories each (strongly agree, agree, neutral, disagree, and strongly disagree).

Questions (1) to (3) contain the primary outcomes, and (4) and (5) include the secondary outcomes. These are summarised in Figure 1.

Patients with CIEDs, except those on warfarin or those with other relevant medical issues (followed up on other clinic consultation schedules), are scheduled for routine clinical follow-ups every 3–6 months. Patient satisfaction surveys are scheduled every 6 months to assess changes in satisfaction levels over time and explore varying trends across device types (‘Survey on telehealth patient experience’ by [name], 2023 [15], modified Korean version 1.3; Table 1). The study is summarised in Figure 1, and the process of the study is also available in Supplementary Table S1.

The primary endpoint will be any MACCE after RM (cardiovascular-related death and hospital admissions related to pre-existing cardiovascular disease), defining variables that are predictive of MACCE and unexpected hospital visits during RM. The secondary endpoints will be patient satisfaction with the time, cost, and quality of care after adopting RM (determined via questionnaires on a 6-month basis) and the staffing/time requirements during RM (measured using electronic medical records).

All files and data generated during the study are stored in a safety deposit box or as copied files secured with passwords accessible only to the investigators. Because this study includes personal identifiers and sensitive information, the data will not be openly accessible. Anonymised study data will be made available to researchers upon reasonable request after the study results are published.

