## 2. Materials and Methods

### 2.1. Study Design

The RemoteVerify (ReVe) study is a multicentre, prospective, observational study that will be conducted at eight university hospitals (St. Vincent’s Hospital, The Catholic University of Korea; Eunpyeong St. Mary’s Hospital, The Catholic University of Korea; Seoul St. Mary’s Hospital, The Catholic University of Korea; Keimyung University Hospital; Kyungpook National University Hospital; Pusan National University Hospital; Yeungnam University Medical Center; Pusan National University Yangsan Hospital) in Korea, targeting 450 patients (each centre will enrol 50 to 70 patients). This sample size was based on the assumption that the 2-year incidence of major adverse cardiac and cerebrovascular events of patients with structural heart diseases is 10% to 15%, with a confidence interval of 95% and a margin of error of 5%. The desired sample size was calculated as 139 to 196 participants per group using G*Power version 3.1.9.7 [16], and similar patients are needed in the two groups that differ in the timing of RM application. Considering an anticipated 10% loss to follow-up during the study period, the total number of participants needed for this study was determined as 442. We rounded this number up to 225 per group. An interim analysis will be conducted using the variables collected by the planned patient enrolment period (24 months). A second interim analysis will be conducted after at least 12 months of follow-up data have been collected. The final analysis will be performed at the study endpoint after all participants have completed the 24-month follow-up. Starting from the interim analysis, subgroup analyses will be conducted based on the type of underlying heart disease (hypertrophic cardiomyopathy/ischaemic cardiomyopathy/dilated cardiomyopathy/others) and the left ventricular ejection fraction (LVEF; <30%, 30–45%, >45%).

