### 2.3. Statistical Analysis

We will compare outcomes before and after RM via paired *t*-tests in the historical group. We will compare the clinical-, RM-, and device-related variables via independent samples *t*-test between the historic and initiating RM groups. Tests for normality will be provided. If data is non-normal, then *t*-tests and means/standard deviations should be avoided, and Mann–Whitney/Wilcoxon and medians/interquartile ranges should be preferred. For the *t*-tests, we will reject the null hypothesis when the two-sided *p*-value is less than 5%. For the analysis of patient baseline data, continuous variables will be presented as means and standard deviations and analysed using *t*-tests or Wilcoxon rank-sum tests. Categorical variables will be presented as frequencies and percentages. For the analysis of satisfaction with the survey, paired *t*-tests (parametric test) or Wilcoxon signed-rank tests (non-parametric test) will be performed. For surveys conducted only after monitoring, ordinal variables will be analysed using the Mann–Whitney U test, and continuous variables will be analysed using chi-square tests. For patients not completing the follow-up, censoring will be based on the last data collected. Cumulative event probabilities will be estimated with adverse health outcomes, such as patient deaths, inpatient admissions, and MACCEs. Hazard ratios and 95% confidence intervals will be generated with Cox proportional hazards models. For subgroup analyses, the interaction term between the prespecified groups, based on the type of underlying heart disease and LVEF, will be evaluated for the primary outcome. Because of the interim analyses, we will adopt the O’Brien–Fleming method for statistical corrections. For all analyses, we will use two statistical software packages: Stata, version 18 (StataCorp LLC, College Station, TX, USA), and R, version 4.05 (R Foundation for Statistical Computing, Vienna, Austria).

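### After enrolment both groups have remote monitoring, so the historical-versus-initiating comparison describes late versus early start and is not evidence that monitoring reduces hospitalisation

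*Protocol article*

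**What the plan says.** Protocol article, section 2.2 (Data Collection), gives the between-group comparison a causal purpose: "They will be compared to patients in the initiating group to determine whether the hospitalisation rate improves with the application of RM".

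The same section defines the groups as "the historical group consisting of patients who already have CIEDs (implanted after January 2020) and have attended outpatient device check-ups" and "the initiating group consisting of patients who will undergo CIED implantation after providing informed consent for participation in this study". It adds that "Patients in the historical group were diagnosed with heart diseases a considerable time before enrolment".

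On exposure, section 2.2 makes no distinction by group: "After informed consent was provided, the patients or their caregivers received a CardioMessenger Smart transmitter (CM) paired with their CIED", and "Daily RM will be initiated the day after device pairing". Section 2.1 (Study Design) describes the contrast as one of timing: "similar patients are needed in the two groups that differ in the timing of RM application". The primary endpoint in section 2.2 is MACCE occurring after RM.

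Section 2.3 (Statistical Analysis) plans paired t-tests of outcomes before and after RM, in the historical group only. Between groups it says "We will compare the clinical-, RM-, and device-related variables via independent samples" t-tests, with a rank test if the data are not normal. For deaths, admissions and MACCE it plans cumulative event probabilities and Cox models, without naming the contrast or the covariates.

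**The concern.** The stated purpose needs time on RM to be compared with time off RM. After enrolment neither group has time off RM. What separates the groups is how long ago the device was implanted, whether the patient had to survive and stay in follow-up to be enrolled, and how advanced the disease is.

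Two errors are then possible. If RM works equally well in both groups, the contrast shows nothing. If RM does nothing, the contrast may still show a difference. Either result could be reported as an answer to the question in section 2.2. The Discussion intends the results to inform guidelines, insurance standards and fees, so the wording matters.

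**Working it through.** **Step 1. Exposure by group and period** (sections 2.1 and 2.2).

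| Period | Historical group | Initiating group |
|---|---|---|
| Before enrolment | Device in place, no RM | No study device yet |
| After enrolment | On RM | On RM, from shortly after implantation |

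The endpoint is counted in the second row, where there is no difference in RM exposure. The only device follow-up without RM is the historical group's time before enrolment.

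**Step 2. The plan's own figure.** Section 2.1 gives 139 to 196 per group for a 10% to 15% two-year MACCE incidence and a 5% margin of error. The one-proportion formula n = 1.96² × p(1 − p) / 0.05² gives:
- p = 0.10: 138.3, rounded up to 139
- p = 0.15: 195.9, rounded up to 196

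Both reproduce. With 10% loss, 196/0.9 rounds up to 218 per group, or 436 in total; the plan's 442 is within 1.4%. The arithmetic is sound, but it sets the precision of one rate per group. It contains no RM effect and no between-group difference.

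**Step 3. A common RM effect cancels.** Let the underlying risks be h (historical) and i (initiating), and let RM multiply both by r. The observed ratio is (h × r)/(i × r) = h/i, whatever r is. If h = i, the ratio is 1.0 for every r.

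As an illustration, take 15% and 10% as the two groups' underlying risks, in either order, with n = 225 per group. The rejection probability of a two-sided 5% test is Φ[(|p1 − p2| − 1.96 × SE0)/SE1], where SE0 is the pooled and SE1 the unpooled standard error. For 15% versus 10%, SE0 = √(2 × 0.125 × 0.875/225) = 0.0312 and SE1 = √((0.1275 + 0.09)/225) = 0.0311.

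| Assumed RM effect in both groups | Risks | Ratio | Probability of rejection |
|---|---|---|---|
| None (r = 1.0) | 15% v 10% | 1.5 | 0.36 |
| 20% reduction (r = 0.8) | 12% v 8% | 1.5 | 0.29 |
| 40% reduction (r = 0.6) | 9% v 6% | 1.5 | 0.23 |

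With assumed risks of 20% and 10% and no RM effect, the probability is 0.85. The ratio follows the difference between the groups and does not respond to RM.

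**Step 4. How far time since implantation can differ.** Initiating patients are observed at 0 to 24 months. A historical patient implanted in early 2020 and enrolled at the end of recruitment in October 2025 enters at about 70 months and is followed to about 94 (70 + 24). That is the extreme, not the typical case: enrolment began in November 2023, and recently implanted patients also qualify.

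As a second illustration, suppose the admission rate in the first 6 months after implantation is k times the later rate. The documents give no value for k. Over 24 months the initiating rate, relative to historical patients already past 6 months, is (0.5k + 1.5)/2, with no RM effect:
- k = 1: 1.00
- k = 1.5: 1.125
- k = 2: 1.25
- k = 3: 1.50

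**Step 5. Which contrasts of RM with no RM exist.** Section 2.3 specifies one, the paired before/after test in the historical group. Every patient in it survived to enrolment, so the death component of MACCE cannot occur in the before period. A second contrast, historical events before RM against initiating-group events on RM, would fit part of section 2.2 but does not appear in section 2.3.

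**The case against.** The strongest reply is that section 2.2 may mean that second contrast. It introduces the historical group to study hospitalisation before and after RM. It says that information on MACCE before RM will be obtained. It then brings in the initiating group because analysing MACCE in the historical group alone would be limiting. On that reading the comparison does set RM against no RM. This stands as a possible intention. However, section 2.3 does not say which historical period is compared with the initiating group, and section 2.2 counts the primary endpoint after RM. The pre-RM contrast would also carry survivor and calendar-time bias unless it were handled explicitly.

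A reader might infer that the study can say nothing about an RM effect. The documents do not support that: the paired before/after test is a specified contrast of RM with no RM, although a limited one.

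A reader might also infer that clinical outcomes will be compared only by unadjusted t-tests. That is not supported either. Section 2.3 plans Cox models for event outcomes, and their covariates may stand in an analysis plan that is not shown. Adjustment is in any case a separate matter, because no covariate creates an exposure difference that is absent after enrolment.

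Finally, the study is partly descriptive: its size rests on precision, and section 2.1 already speaks of timing. That is fair. It is also why the causal sentence in section 2.2 is out of line with the rest of the design.

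**Conclusion.** The concern holds for the comparison made after enrolment. As the article defines exposure and endpoint, that comparison describes late versus early start of RM, confounded by time since implantation, survival to enrolment and disease stage. It supports no claim of RM efficacy. This part needs no assumed figures beyond the same proportional RM effect in both groups; if the effect differed, the contrast would show only how it varies with timing, still mixed with those confounders.

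The size of a spurious difference cannot be known from the documents. The rejection probabilities of 0.36 and 0.85 rest on assumed group risks, and the ratio of 1.25 on an assumed doubling of early admissions. They show that such a difference is possible; they do not predict it.

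The contrast that could address RM between the groups is not specified, and the one that is specified, within the historical group, is limited by survival to enrolment.

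**What to change.** 1. Reword section 2.2 so that the comparison of the two groups after RM starts is descriptive, of the timing of RM start, and is not offered as evidence of an RM effect.

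2. Specify the between-group RM contrast in section 2.3: initiating-group months on RM against historical-group months before RM, at the same time since implantation. In practice this uses the part of each historical patient's pre-RM time that falls within the first 24 months after implantation. Restrict the outcome to non-fatal cardiovascular admissions, because death cannot occur in the pre-RM period of an enrolled patient. Use a rate or recurrent-event model.

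3. Control confounding with a few prespecified variables or a propensity score. At the plan's 10% to 15% incidence, 225 initiating patients give about 23 to 34 with an event (225 × 0.10 = 22.5; 225 × 0.15 = 33.75), and the pre-RM event count is not given. Time since implantation should be handled by alignment. Its value at entry is near zero for every initiating patient and positive for every historical one, so adjusting for it has no overlap to work with.

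4. State the remaining limits. Historical pre-RM months come only from patients who survived and stayed in follow-up, and they run from 2020, whereas initiating months start in late 2023 at the earliest. State the survivor limit for the paired before/after test too.

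Cost: softer efficacy wording and some extra modelling. Implantation dates are among the baseline data, and events before RM are already to be obtained, so no new data source is needed.

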Eligible study participants will need to meet the following criteria: patients (1) aged 20 years or older with (2) an LVEF below 40% or a structural heart disease confirmed via cardiac imaging, (3) an implantable cardioverter–defibrillator (ICD) or a cardiac resynchronisation therapy (CRT) device compatible with Biotronik Ltd. (Berlin, Germany) wireless monitoring devices, and (4) a predicted life expectancy of more than 6 months, (5) capable of understanding and completing the simple consent form, and (6) never having been enrolled in clinical trials that involve RM before. Patients will be informed that if they want to withdraw their consent to this study, they can stop participating in this clinical trial, and their data will be collected until the withdrawal date. Exclusion criteria are as follows: (1) patients with a life expectancy of 6 months or less, (2) patients with cognitive impairment who are unable to understand the information regarding wireless monitoring or who are unable to provide consent, and (3) patients currently participating in another clinical trial that may be affected by the implementation of wireless monitoring. Patients who have previously participated in clinical trials, those who are currently participating in a clinical trial that the investigator judges will not affect or be affected by this trial, and those who are participating in other observational studies are eligible for this study. If the patient wishes to discontinue participation in the study or dies within 6 months of participation (to be noted separately), they will be considered withdrawn from the study.

Informed consent will be obtained from each participant included in the study. Details of the study protocol are available at ClinicalTrials.gov (study ID: NCT05971225). Patient enrolment started in November 2023 at two centres (40 and 10 patients were enrolled in St. Vincent’s Hospital and Eunpyeong St. Mary’s Hospital, respectively, as of 1 August 2024) after Institutional Review Board approval (VC23DIDI0148; approval date: 11 July 2023) and will continue until October 2025. Follow-up data will be acquired for 24 months after enrolment. We plan to collect the final data in December 2027, and the results of the ReVe study will be published in 2028.

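### Enrolment precedes implantation in the initiating group but follows it in the historical group, so implant admissions and most early implant-related events count against the initiating group in the between-group comparison

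*Protocol article*

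**What the plan says.** The two groups are defined in section 2.2 of the protocol article. One is "the historical group consisting of patients who already have CIEDs (implanted after January 2020) and have attended outpatient device check-ups". The other is "the initiating group consisting of patients who will undergo CIED implantation after providing informed consent for participation in this study". Each is planned at 225 patients. Section 2.1 sets the window: "Follow-up data will be acquired for 24 months after enrolment".

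What is captured in that window is the first item of the numbered list in section 2.2: "Collecting data from all visits or admissions during the study period, classified as device-related, patient cardiovascular condition-related, or non-cardiovascular condition-related events". The same section gives these data their status: "Questions (1) to (3) contain the primary outcomes, and (4) and (5) include the secondary outcomes". The second list item describes MACCE broadly and includes admissions for cardiac causes and a residual category of further cardiac events.

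Later in section 2.2 the primary endpoint is narrower: MACCE occurring after RM, made up of cardiovascular death and admissions linked to cardiovascular disease the patient already had. RM starts the day after the transmitter is paired with the device.

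Section 2.2 plans to compare historical with initiating patients to see whether hospitalisation improves with RM. Section 2.3 says: "We will compare the clinical-, RM-, and device-related variables via independent samples" *t*-tests, with Mann–Whitney as the alternative, and adds Cox models. The article states no rule for the implant admission and no common starting point relative to implantation.

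**The concern.** The groups sit on opposite sides of the operation when their clocks start. An initiating patient's 24 months include the implant stay and the weeks in which lead, pocket or other procedure-related problems are most likely to bring the patient back. A historical patient has usually passed that period, and must have done well enough to attend device check-ups.

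The two windows are then compared on admissions and device-related variables. A difference created by the surgery would be read as a difference created by the timing of RM. It runs against the initiating group, so RM from implantation could look unhelpful or harmful. The Discussion expects the results to support guidelines, policy and insurance standards, so this misreading would matter.

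**Working it through.** **Inputs from the article.** 225 patients per group; 10% loss to follow-up; assumed 2-year MACCE incidence p of 10% to 15%; two-sided 5% level; 24 months from enrolment.

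**The plan's own figure.** n = 1.96² × p(1 − p) / 0.05² gives 138.3, so 139, at p = 0.10, and 195.9, so 196, at p = 0.15. Both match section 2.1. Allowing for loss, 196 / 0.9 = 217.8, so 218 per group and 436 in total, close to the stated 442. The sizing is for the precision of a single proportion, not for a test between groups. This point disputes none of these figures; p is only borrowed below.

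**Step 1: all admissions.** If the implant stay is counted, each initiating patient gains exactly one admission: 225 extra in that group. The article gives no background admission rate. Assuming m = 0.15 to 1.0 admissions per patient over 24 months in both groups, with no effect of RM timing, the rate ratio (1 + m)/m is 1.15/0.15 = 7.7 down to 2.0/1.0 = 2.0.

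**Step 2: MACCE after RM.** The implant stay itself largely drops out. Let x be the proportion of initiating patients with an early implant-related admission that is counted as MACCE. The article does not give x, so it is an assumption. With no true effect:

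- initiating-group risk t = 1 − (1 − p)(1 − x)
- spurious hazard ratio = ln(1 − t) / ln(1 − p)
- illustrative false-positive rate from z = ln(HR) × √(D/4), with D = 202 × (p + t) and 202 ≈ 225 × 0.9

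| x | p | t | Hazard ratio under no effect | False-positive rate |
|---|---|---|---|---|
| 0% | 10% or 15% | equal to p | 1.00 | 5% |
| 2% | 10% | 11.8% | 1.19 | 9.0% |
| 2% | 15% | 16.7% | 1.12 | 7.6% |
| 5% | 10% | 14.5% | 1.49 | 28.7% |
| 5% | 15% | 19.25% | 1.32 | 20.7% |

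Example, x = 5% and p = 10%: t = 1 − 0.90 × 0.95 = 0.145; ln(0.855)/ln(0.90) = 1.49.

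The last column shows what a two-sided 5% hazard-ratio test between the groups would do. Section 2.3 does not say that the Cox models make that comparison.

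**Step 3: would a time-since-implantation model serve?** Initiating patients are implanted after consent and followed 24 months from enrolment, so they contribute less than 24 months since implantation. Enrolment began in November 2023, so any historical patient implanted before November 2021 enters more than 24 months after implantation and shares no risk set with the initiating group. Eligible implants go back to January 2020, so a large part of the historical group could be lost from the contrast.

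**The case against.** The strongest reply is that the primary endpoint already excludes most of this. It counts only MACCE after RM and only admissions linked to existing cardiovascular disease, and the event classes separate device-related from cardiovascular-condition-related events. On that wording the implant stay is out, and many lead or pocket problems arguably are too. That stands, and it limits the point for the primary endpoint. It does not help the comparison of all admissions and of device-related variables, which are collected over the whole study period. The broader description of MACCE in the numbered list could also let early implant-related admissions back in.

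A reader might set 225 implant admissions beside the 22.5 to 33.75 patients expected to have a MACCE and infer that 87-91% of initiating-group events are artefact (225/258.75 and 225/247.5). The documents do not support that: it mixes admissions with MACCE patients and ignores the after-RM limit.

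A reader might also infer that the historical window contains no implant complications at all. No minimum time since implantation is set, so a recently implanted historical patient can still have one in follow-up.

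Two further uncertainties stand. The article does not say how soon pairing follows implantation; late pairing would leave fewer early events after RM. Nor does it say how far back the historical group's pre-RM record reaches. If it reaches implantation and is the comparator, both sides include an implant period.

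Finally, a condensed article may leave the handling of the index admission to the full protocol. But the point does not rest on that silence: the stated group definitions, enrolment-based window and planned comparison produce the imbalance together.

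**Conclusion.** The concern holds for the prospective between-group comparison of admissions and device-related variables. Following the text as written adds one implant admission per initiating patient, and most early implant-related events, to one side. The direction, against the initiating group, follows from the design.

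For MACCE after RM the bias is smaller and conditional. Its size cannot be derived from the article. It is nil if no early implant-related admission is classed as MACCE, and a hazard ratio of about 1.1 to 1.5 under no true effect if 2-5% of initiating patients have one that is. These values rest on the assumed x, on the planned 10-15% incidence and on prompt pairing. They should not be read as a forecast, nor as a claim that the primary endpoint is invalid. The change should be made before the groups are compared.

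**What to change.** In sections 2.2 and 2.3:

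1. State that the implant admission is not an admission outcome, a MACCE or a device-related event.
2. For between-group comparisons of admissions, MACCE and device-related events, prespecify one of two rules. Either leave out events classed as related to the implant procedure, or start at-risk time in both groups after the same short interval since implantation. Under the second rule, a historical patient enrolled beyond the interval starts at enrolment, and a recently implanted one starts when the interval ends. Admissions are then compared per unit of at-risk time.
3. Report the earlier or procedure-related events separately and descriptively, as implant-related harms.
4. Keep an analysis from RM start as a sensitivity analysis.

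A Cox model on time since implantation with delayed entry should not be the main analysis, given the lack of overlap shown above. Starting the initiating clock at the first outpatient device check is also costly: with visits every 3–6 months it could drop 3/24 to 6/24 of follow-up (12.5-25%).

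The cost of the proposed change is low. Implantation date and event class are already collected, although the first rule needs a procedure-related flag within the existing classes. The downside is somewhat fewer early events and a little less follow-up time in the initiating group's comparison, including any early events that RM might have influenced.
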